## Effectiveness evaluation

8

The primary efficacy end point is the all-cause 30-day mortality of patients in clinically evaluable and microbiologically evaluable populations.

The secondary efficacy endpoints are as follows: (1) the proportion of patients with a total response (composite endpoint consisting of clinical cure and microbiological response) in the clinically evaluable population at the end of treatment (days 5–14) and the test of cure visits (days 12 ± 2); (2) the proportion of total responsive patients in the microbiome-evaluable population at the end of treatment and the test of cure visits; (3) the proportion of microbiologically evaluable patients in the population with a total response to each pathogenic bacterium at the end of treatment and the test of cure visits; (4) the total response proportion of patients with drug-resistant bacterial infections in the microbiome-evaluable population at the end of treatment and the test of cure visits; (5) ICU hospitalization time and expenses; (6) quality of life outcomes or functioning after ICU discharge as assessed by application of the EuroQol-5D and Barthel Index scales; (7) changes in Sequential Organ Failure Assessment (SOFA) scores, reflecting the impact of the treatment on organ dysfunction over time; and (8) time to clinical improvement, measured from the start of treatment until the first observation of significant improvement in clinical status.

Given the variable susceptibility of MDR pathogens to tetracyclines, our study protocol will include analyses stratified by bacterial species. Specifically, subgroup analyses will be conducted for CRAB and CRE to gain a deeper understanding of the comparative efficacy of eravacycline versus tigecycline.

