
### Criteria for early withdrawal from treatment

4.3

Early withdrawal from treatment refers to withdrawal from the study treatment before the completion of the treatment course. Patients who withdraw from treatment early are not considered withdrawn from the study early and should continue to complete the follow-up visit process. The study will employ an intention-to-treat analysis, which includes all patients who were initially randomized to receive the study drug, regardless of whether they completed the full course of treatment. This approach ensures that the analysis reflects the provided treatment options’ real-world effectiveness. The criteria for early withdrawal from treatment are as follows:

The patient or their authorized person requests to withdraw from treatment;Patients whose conditions worsen or do not improve after 72 h of continuous use of the investigational drug and who have been determined by the researcher to no longer benefit from continued use of the investigational drug;After the investigational drug is applied, if the sample culture strain is resistant to the drug, the clinical efficacy is evaluated by the researcher as persistent or progressive;Individuals who experience intolerable adverse events/serious adverse events and for whom it has been determined by the researcher that continuing to use the investigational drug would pose a greater risk to the patient than its benefits;Cases in which protocol violations occur, such as receiving other effective antimicrobial treatments (excluding those specified in the protocol) or other concomitant medications prohibited by this protocol during the study period, which, in the judgment of the researcher, might seriously affect the elimination, metabolism, or efficacy evaluation of the investigational drug;Other situations that require early withdrawal from treatment.

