### Exit criteria

4.4

All patients who signed a written informed consent form and were screened as qualified to enter the study had the right to withdraw at any time. The exit criteria were as follows:

The patient or their authorized person refuses to continue the study or voluntarily withdraws informed consent;Patient death;Patients who are lost to follow-up;Poor compliance, no longer accepting the medication or testing before completing all studies, or inability to adhere to the study protocol to complete the study;Other situations that the researchers believe require withdrawal.

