## Population definition

7

The microbiologic modified intention to treat (mITT) population will include all patients with a confirmed diagnosis of complex abdominal infections (cIAIs) and positive infection source samples and/or blood sample cultures at baseline [excluding pathogens not expected to respond to either trial drug, such as nonfermenting gram-negative bacilli (e.g., *P. aeruginosa*, fungi, or mycobacteria)]. The mITT population will be used for demographic and baseline purposes.Clinical evaluation (CE) population: In the mITT population, researchers will follow the requirements of important components of the study protocol [such as cultivating baseline pathogenic gram-negative pathogens (reported in infection source samples and/or blood samples)], excluding those patients with pathogens (*P. aeruginosa*) who do not respond as expected to the investigational drug. This population will be used for clinical efficacy and all-cause mortality analysis.Microbiologically evaluable (ME) population: In the mITT population, individuals who have completed the study in accordance with important components of the study protocol and obtained baseline pathogenic gram-negative pathogens (reported in infection sources and/or blood samples) are expected to respond to the investigational drug. This population will be used for clinical efficacy, microbiological efficacy, comprehensive efficacy, and all-cause mortality analyses.Safety analysis (SS) population: Patients who have received at least one dose of the investigational drug during the clinical study period. The safety analysis population will be used for the analysis of safety data.

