The intention to improve treatment will be analyzed based on microbiology, including all randomized subjects, who will be evaluated within their randomized groups. For continuous numerical variables, the quantity, mean, median, standard deviation, minimum, maximum, and coefficient of variation (CV, if applicable) will be determined after an independent sample t test or Wilcoxon rank sum test. The categorical variables will be reported as rates (percentages) and will be analyzed using the Pearson X^2^ test or Fisher’s exact probability method. The baseline will be defined as the last nonmissing observation data collected before the first use of the study drug. The Shapiro–Wilk test and QQ plot in SAS will be used to check the normality of the data. All the statistical analyses will be performed using SAS software (version 9.1 or higher; SAS Institute), and all the statistical inferences will be conducted using a two-sided test with a statistical significance level of 0.05. Confidence intervals (CIs) will be calculated and reported for all endpoints, thereby providing a comprehensive interpretation of the clinical relevance and statistical significance of the findings. Missing data will be classified as response uncertainty, and in the analysis of the microbiological intention-to-treat population, this will be considered treatment failure.

We will calculate and report CIs for all secondary endpoints, such as treatment response rates, to provide a comprehensive interpretation of the clinical relevance and statistical significance of our findings.

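### Primary 30-day mortality is placed only in the two evaluable populations, against the stated intention-to-treat analysis of all randomised patients

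*Protocol article*

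**What the plan says.** Four parts of the protocol article bear on who is counted in the primary analysis.

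- **Section 8 (Effectiveness evaluation)**, in line with the abstract: "The primary efficacy end point is the all-cause 30-day mortality of patients in clinically evaluable and microbiologically evaluable populations".
- **Section 7 (Population definition)** assigns mortality to CE and ME and to no other set. For the microbiological modified intention-to-treat (mITT) set it says: "The mITT population will be used for demographic and baseline purposes". CE begins: "In the mITT population, researchers will follow the requirements of important components of the study protocol". ME consists of "individuals who have completed the study in accordance with important components of the study protocol" who also have a baseline gram-negative pathogen expected to respond. No all-randomised set is defined.
- **Section 4.3 (Criteria for early withdrawal from treatment)**: "The study will employ an intention-to-treat analysis, which includes all patients who were initially randomized to receive the study drug", whether or not the course was completed. Patients who stop treatment early stay in follow-up.
- **Section 11 (Statistics)** describes a microbiology-based intention-to-treat analysis "including all randomized subjects, who will be evaluated within their randomized groups".

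Section 4.4 (Exit criteria) lists these among the ways of leaving the study: "Patient death;Patients who are lost to follow-up;Poor compliance, no longer accepting the medication or testing before completing all studies". Table 3 lists survival at 30 days after randomisation among the outcome data.

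**The concern.** The stated principle and the stated primary population do not match. Under sections 4.3 and 11 every randomised patient is analysed as allocated. Under sections 7 and 8 the primary result comes from subsets of culture-positive patients, at least one of which is restricted further by what happened after randomisation.

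The restriction to baseline culture is a baseline feature and mainly costs numbers. The risk of bias lies in the adherence and completion conditions. The reasons for stopping treatment in section 4.3 include no improvement at 72 hours, a resistant culture with persistent disease, and use of other effective antimicrobials. All are related to outcome, may be related to treatment, and several rest on the researcher's judgment. Section 5 accepts that clinicians may know the allocation.

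The ME wording also sits badly with its use. A set defined by completing the study is asked to measure mortality, while section 4.4 treats death as an exit. The exit for poor compliance, which covers patients who no longer accept the medication, likewise works against section 4.3, which keeps them in follow-up.

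At stake is the noninferiority conclusion on death. Deaths missing from one arm more than the other could move the ratio to the wrong side of the margin.

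**Working it through.** **1. Is the planned sample size sound in itself?** Inputs from section 11: control mortality p2 = 0.187; true ratio 0.95, so p1 = 0.95 × 0.187 = 0.17765; margin R0 = 2; one-sided α = 0.025; power 80%; 1:1 allocation. The method is the Farrington-Manning score test for a ratio.

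- Constrained estimate under p1 = 2·p2: solve 2q² − [R0(1 + p2) + 1 + p1]q + R0(p1 + p2) = 0, that is 2q² − 3.55165q + 0.7293 = 0. This gives q1 = 0.2370 and q2 = q1/2 = 0.1185.
- s0 = √[q1(1 − q1) + 4·q2(1 − q2)] = 0.7737
- s1 = √[p1(1 − p1) + 4·p2(1 − p2)] = 0.8685
- d = 2 × 0.187 − 0.17765 = 0.19635
- n per arm = [(1.960 × 0.7737 + 0.8416 × 0.8685)/0.19635]² = 131.0

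That is 131 per arm, N = 262. Inflating, 262/0.9 = 291.1, rounded up to 292 (146 per arm). Both planned figures reproduce, so the problem is the analysis set and not the arithmetic.

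**2. Power when only evaluable patients count.** Power = Φ[(d√n − 1.960·s0)/s1], with n = 146 × evaluable share. The article gives no evaluable share, so the shares below 100% are assumptions.

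| Evaluable share | n per arm | Power | Randomised to keep 262 evaluable |
|---|---|---|---|
| 100% | 146 | 83.8% | 262 |
| 90% | 131.4 | 80.1% | 292 |
| 80% | 116.8 | 75.7% | 328 |
| 70% | 102.2 | 70.5% | 375 |
| 60% | 87.6 | 64.4% | 437 |

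The 10% allowance would have to absorb culture-negative patients, excluded pathogens and protocol deviations together.

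**3. Bias when deaths are left out.** If a fraction g of the deaths in an arm with mortality p is excluded, observed mortality is p(1 − g)/(1 − pg), because the excluded patients leave the denominator too. Take a true ratio at the margin: 0.374 against 0.187. The values of g are assumptions.

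- Control g = 0, eravacycline g = 0.25: 0.374 × 0.75/(1 − 0.374 × 0.25) = 0.2805/0.9065 = 0.309. Ratio 0.309/0.187 ≈ 1.65. Starting from 131 per arm, the log-ratio approximation puts the chance of declaring noninferiority at about 13% instead of the nominal 2.5%.
- Control 0.10, eravacycline 0.30: ratio 1.72, chance about 9%.
- Control 0.25, eravacycline 0.50: ratio 1.56, chance about 14%.
- Both arms 0.25: ratio 2.10.
- Control 0.25, eravacycline 0: control mortality 0.14025/0.95325 = 0.147, so the ratio is 0.374/0.147 ≈ 2.54.

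The direction therefore depends on which arm loses more deaths. The first three cases favour noninferiority and the last two work against it.

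**The case against.** **Evaluable sets are customary in noninferiority trials.** They are, but alongside an all-randomised analysis. Here they take its place for an outcome that can be established in nearly everyone.

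**Sections 4.3 and 11 state general principles.** A reader might infer several rival definitions of the primary population. The documents do not support that. Only the abstract and sections 7 and 8 name a population for mortality, and the section 11 sentence is visibly garbled. What stands is a conflict between the announced principle and the population assigned.

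**ME cannot be meant to exclude deaths.** A reader might infer that ME mortality is nil by construction. Section 7 gives ME a mortality use and Table 3 collects survival, so the authors can hardly intend this. The natural reading is a per-protocol set. It remains a wording defect in a primary population.

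**CE is less clearly affected.** Its sentence is garbled, names only baseline culture features as examples, and has no completion condition. Selection on adherence in CE is an inference from the text.

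**Blinding.** Section 5 adds a blinded clinical assessor and blinded data analysts. That helps, but the article does not say who decides membership of CE or ME.

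**Points that do not belong here.** The rule in section 11 that treats missing data as failure is written in terms of response and does not say that unknown vital status counts as death. How to act if CE and ME disagree may be settled in an analysis plan that is not shown.

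**An all-randomised analysis has a cost.** It brings in culture-negative patients and pathogens not expected to respond, which may pull the ratio towards 1. This stands and is a reason to report CE and ME beside it.

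**Conclusion.** The point holds. The article announces an intention-to-treat analysis of all randomised patients and then assigns primary mortality only to CE and ME. ME certainly, and CE apparently, selects on events after randomisation that are related to outcome. ME's completion condition conflicts with its use for mortality.

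The size cannot be fixed from the documents. The observed ratio of 1.65 for a true 2.0 rests on an assumed, one-sided loss of a quarter of eravacycline deaths; other assumed splits give ratios from 1.56 to 2.54. The loss of power depends on an evaluable share that the article does not state. The 83.8% for all 292 patients assumes the article's own mortality rates and complete vital status. None of this shows that deaths will be dropped. It shows that the wording permits it and that the primary population needs to be settled before analysis.

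**What to change.** - In section 8 and the abstract, make the primary analysis 30-day all-cause mortality in all randomised patients as allocated. Add that set to section 7 and bring the section 11 sentence into line.
- Keep CE and ME as supportive mortality analyses, reported beside the primary result because of the possible dilution. Reword the CE definition so that its conditions can be read.
- State in section 7 that death by day 30 is an observed outcome and never removes a patient from a mortality population.
- Amend section 4.4 so that non-compliance does not end collection of 30-day vital status, consistent with section 4.3. Death naturally ends follow-up and can stay in the list.

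The cost is protocol wording and a 30-day vital-status check that Table 3 already provides for. The sample size need not rise: with complete vital status, power at 146 per arm is above the planned 80%.

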### Exclusion criteria

4.2

Patients who are known to have allergies to any excipients containing eravacycline, tigecycline, tetracycline, or investigational drug formulations;Patients with intra-abdominal lesions that are unlikely to have infectious primary causes, such as inflammatory bowel disease, liver abscess, abdominal wall abscess, intestinal obstruction without perforation, or ischemic bowel without perforation;Patients with intra-abdominal infections suspected to be caused by fungi, parasites, viruses, or pulmonary tuberculosis, except in cases of upper intestinal perforation where empirical coverage of fungi is often given, will not be excluded;The exclusion criteria related to antibiotics are as follows: a. within 72 h prior to randomization, effective antimicrobial therapy was used for >24 h [however, patients with clear baseline pathogens and treatment failure after antibiotic treatment for at least 72 h may be enrolled]; b. cases in which cIAI is known to be caused by a pathogen resistant to one of the investigational drugs; c. patients who receive treatment for the current infection with investigational drugs or similar drugs; or d. in addition to research drugs, it is also necessary to use nonresearch antibacterial drugs in combination;An anticipated need for systemic antibiotic treatments lasting more than 14 days;Obvious liver disease, liver function damage (Child–Pugh C grade), or possible signs of liver disease and/or abnormal laboratory test results: a. ALT or AST > 5xULN; b. total bilirubin>3xULN;Patients with congenital or acquired immunodeficiency diseases, those who have received organ transplantation within the previous year of enrollment, or those who have received immunosuppressive drug treatment within 30 days before enrollment;Patients who are within 7 days prior to randomization or who are expected to use potent CYP3A inducers, such as phenytoin sodium, rifampicin, or carbamazepine, during the study period;Patients with systemic malignant tumors that require chemotherapy, immunotherapy, radiation therapy, or antitumor treatment within the 3 months prior to total organic compound (TOC) visits;Pregnant women, lactating women, or those with a fertility plan within 2 weeks after the end of the study;Patients who have participated in clinical trials of other drugs or medical devices within 1 month prior to screening;Patients who are expected to have a survival time or treatment intention of less than 6– to 8 weeks; and.Patients who, as determined by the researchers, do not meet the criteria for inclusion in clinical trials for various reasons, such as concomitant brain herniation, acute myocardial infarction, pulmonary embolism, or ECMO treatment.

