## Study drug management

6

Two research drugs (eravacycline and tigecycline) have been approved for marketing by the National Medical Products Administration in China. The approved indications include complex abdominal infections in adults. Therefore, this study strictly followed the approved dosage for intravenous administration according to the instructions. The recommended dose of eravacycline is 1 mg/kg, which is administered every 12 h, and the duration of intravenous infusion is approximately 60 min. The recommended dosage for tigecycline is 100 mg for the first dose, followed by 50 mg every 12 h for intravenous infusion lasting 30–60 min. All the study treatments will last for 4–14 days. The total duration of treatment will be determined by clinical doctors based on the severity of the infection, patient clinical response, imaging studies, progress in bacteriology, and when possible, consultation with surgical and infectious disease experts. For patients with renal dysfunction or those who are undergoing hemodialysis, the dosage of the investigational drug does not need to be adjusted. The dose adjustment for patients with liver function impairment is shown in Table 1.

**Table 1 tab1:** Dose adjustment of the study drug.

	Eravacycline	Tigecycline
Normal hepatic function	1 mg/kg q12h	50 mg q12h (First dose 100 mg)
Child–Pugh A	1 mg/kg q12h	50 mg q12h (First dose 100 mg)
Child–Pugh B	1 mg/kg q12h	50 mg q12h (First dose 100 mg)
Child–Pugh C	On the first day, 1 mg/kg every 12 h Starting the next day, 1 mg/kg every 24 h	25 mg q12h (First dose 100 mg)
Renal insufficiency	No adjustment required	No adjustment required
Continuous renal replacement therapy	No adjustment required	No adjustment required

Resistance to tigecycline will be routinely tested as part of the study protocol. In cases where resistance is identified, the study will manage crossover treatments based on predefined criteria, and data on eravacycline resistance will also be collected and tested routinely to guide clinical decisions and ensure patient safety.

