If a patient shows clinical improvement after ≥4 days of intravenous study treatment, the treatment can be stopped. If *Pseudomonas aeruginosa* is suspected or isolated, open-label amikacin or gentamicin can be added to any protocol based on the researcher’s judgment. Antifungal therapy is prohibited unless there is clear evidence of a pathogen. The research plan aims to minimize the likelihood of previous use of other antibiotics, which may confound the evaluation of treatment efficacy.

During the administration process, circulatory and respiratory functions will be continually monitored, and airway assistance measures, artificial ventilation, and other resuscitation devices will be readily accessible. Symptoms and fluctuations before and after administration will be recorded in the patients’ and nurses’ records. When adverse reactions occur, the symptoms, medication duration, dosage, and intervention measures will be recorded.

Eravacycline was acquired from Everest Medicine (Singapore) Pte Ltd., specification 50 mg, batch number AT3072B; tigecycline was obtained from CTTQ PHARMA, specification 50 mg, batch number 230504115.

The protocol will include a comprehensive screening process for known CYP3A4 inducers and inhibitors (Appendix). Patients with potent CYP3A4 inducers will be excluded from the study based on exclusion criteria. Patients on moderate or weak CYP3A4 inducers will be monitored closely, but no dosage adjustment will be made unless deemed necessary by the treating physician. In addition, patients on CYP3A4 inhibitors will be evaluated for potential drug–drug interactions, and appropriate measures will be taken to minimize the risk of adverse effects.

The protocol prohibits using medications that may interfere with the study drug’s efficacy or safety profile. This includes antibiotics with similar mechanisms of action or known to affect the study outcomes. A comprehensive list of prohibited medications is included in the study protocol’s Appendix, which will be provided to all participating sites and made available to investigators and participants upon request (Appendix).

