Outcome data	Survival at 30 days post randomization Date of death or discharge Total response (composite endpoint consisting of clinical cure and microbiological response) at the end of treatment and the test of cure visits Length of ICU stay and costs Protocol violations and adverse events Reasons for trial withdrawal

cIAI, complicated intra-abdominal infection; ICU, intensive care unit; APACHE, Acute Physiology and Chronic Health Evaluation; SOFA, Sequential Organ Failure Assessment; CRP, C-reactive protein; PCT, procalcitonin.

An independent Data Safety and Monitoring Board (DSMB) will be constituted to further enhance the safety and integrity of the study. The DSMB, comprising experts with pertinent knowledge and experience, will operate independently of the study team. Its remit is to conduct regular reviews of the accumulating trial data, to ensure the safety of participants and the validity of the trial results. The DSMB will have the authority to recommend to the sponsor whether to continue, modify, or stop the trial, based on its data review insights.

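### The test-of-cure window (days 10–14, no anchor stated) lies wholly inside the end-of-treatment window (days 5–14), so for courses of 10 days or more the test of cure need not fall after treatment ends

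*Protocol article*

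**What the plan says.** Section 8 (Effectiveness evaluation) lists as its first secondary endpoint the proportion with total response "at the end of treatment (days 5–14) and the test of cure visits (days 12 ± 2" days, counted from a point that is not stated. Secondary endpoints 2 to 4 use the same two visits for the microbiologically evaluable patients, for each pathogen, and for drug-resistant infections. Table 3 (section 10) lists the item to be collected: "Total response (composite endpoint consisting of clinical cure and microbiological response) at the end of treatment and the test of cure visits".

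Section 6 (Study drug management) sets the permitted course: "All the study treatments will last for 4–14 days". Length is individual: "The total duration of treatment will be determined by clinical doctors based on the severity of the infection", together with response, imaging and bacteriology. It may end early: "If a patient shows clinical improvement after ≥4 days of intravenous study treatment, the treatment can be stopped". Section 4.2 excludes only "An anticipated need for systemic antibiotic treatments lasting more than 14 days", so courses of up to 14 days are in scope.

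Section 5 (Test group) acknowledges that treating clinicians may know the allocation and adds a blinded clinical assessor.

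The primary endpoint has its own clock. Table 3 gives it as "Survival at 30 days post randomization".

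**The concern.** A test-of-cure visit is meant to show that the response lasts once the drug has stopped. Section 11.2 compares the arms at different visit times, which presumes that end of treatment and test of cure are distinct. With the windows as printed, the second visit can fall on the same day as the first or before it when the course is long.

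Two things are at stake. First, the same endpoint would be a durable off-drug response in a patient treated briefly and an on-treatment response in a patient treated for two weeks. Longer courses go with more severe infection, because severity is one of the stated grounds for choosing the length. Second, if the arms differ in course length, they will differ in how many patients are still on drug at test of cure. That difference could appear as a treatment effect or hide one.

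**Working it through.** **Inputs**
- End-of-treatment (EOT) window: days 5–14 (section 8).
- Test-of-cure (TOC) window: day 12 ± 2 (section 8).
- Course length L: 4 to 14 days (section 6).
- Assumption, since the article gives no anchor: day 1 is the first treatment day and also the day of randomisation, so the last treatment day is day L.

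The article states no TOC-to-EOT interval, so there is no printed figure to reproduce.

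**Step 1: the windows.** TOC runs from 12 − 2 = 10 to 12 + 2 = 14. The overlap with EOT runs from max(5, 10) = 10 to min(14, 14) = 14. Every TOC day is therefore also a permitted EOT day.

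**Step 2: visit to visit.** TOC minus EOT is lowest at 10 − 14 = −4 days and highest at 14 − 5 = +9 days.

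**Step 3: time off drug at TOC.** For course length L the interval is 12 − L at the nominal visit, and runs from 10 − L to 14 − L over the window.

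| Course L (days) | Nominal TOC minus last treatment day | Range over the window | TOC days on or before the last treatment day (of 5) |
|---|---|---|---|
| 4 | +8 | +6 to +10 | 0 |
| 7 | +5 | +3 to +7 | 0 |
| 9 | +3 | +1 to +5 | 0 |
| 10 | +2 | 0 to +4 | 1 |
| 11 | +1 | −1 to +3 | 2 |
| 12 | 0 | −2 to +2 | 3 |
| 13 | −1 | −3 to +1 | 4 |
| 14 | −2 | −4 to 0 | 5 |

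Courses of 4–9 days always have TOC after the last dose, by 1 to 10 days. A 10-day course can at most touch the last treatment day. From 11 days TOC can come before the last dose. At 14 days no day in the window lies after treatment. The whole range is 14 − 4 = +10 to 10 − 14 = −4.

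**Step 4: sensitivity to the day count.** If the first treatment day is numbered 0, every interval rises by one day, and a 14-day course gains a single off-drug TOC day (day 14). If dosing starts late on day 1 and runs into day L + 1, every interval falls by one day. The pattern is the same.

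**Step 5: the other anchor.** If day 12 ± 2 were counted from the last dose, TOC would fall between about day 4 + 10 = 14 and day 14 + 14 = 28, and the overlap would disappear.

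**Step 6: what is not touched.** The sample size in section 11 uses control mortality 18.7%, true ratio 0.95, margin 2, one-sided 0.025 and 80% power. A Farrington–Manning score calculation on those inputs returns the stated 262, and 262 / 0.9 rounds up to 292. No TOC quantity enters it.

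**The case against.** The strongest reply is that the article never says what day 12 ± 2 is counted from. A count from the last dose would remove the problem, and the full protocol or the flow chart may say so. The missing anchor is conceded, and the finding depends on it. But the two windows stand side by side in one phrase. Days 5–14 can only be counted from randomisation or start of treatment, and nothing signals a change of clock for the second window. If the last-dose count was intended, the printed text still needs correcting, because the two readings put the visit on days 10–14 or on about days 14–28.

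The remaining objections limit how far the point goes:

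- A reader might infer that cure will generally be assessed on drug. The documents do not support that. Courses of 4–9 days are clear, a 10-day course has four of five window days off drug, and treatment may stop early on improvement. No distribution of course length is given, so the share affected could be small.
- A reader might infer that the secondary comparison is biased. No difference in duration between arms is documented, and its direction would be unknown. The blinded assessor in section 5 protects the judgement of response. Nothing says that this person sets the duration, so the route through duration stays open, but only as a possibility.
- A reader might see a contradiction between the day-5 lower limit for EOT and the 4-day minimum course. A visit on the day after a 4-day course explains it, so it is not part of this point.
- Endpoints 1–4 are also read at EOT, and the primary endpoint is unaffected. That stands, and it lowers the severity.

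**Conclusion.** As printed, sections 6 and 8 do not fit together. The TOC window lies wholly within the EOT window, and for courses of 10 days or more an off-drug test of cure is not assured. For a 14-day course it is impossible when day 1 is the first treatment day. Across permitted courses the off-drug interval at TOC spans about 14 days (+10 to −4), so secondary endpoints 1–4 at that visit are not one quantity across patients. Bias between arms is possible because duration is set by clinicians who may know the allocation, but it is not shown.

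The conclusion rests on counting both windows from randomisation or start of treatment. How many patients it concerns cannot be worked out from the article. Thirty-day mortality and the sample size do not depend on it. Severity: should-fix, because only secondary endpoints are involved.

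**What to change.** Reconcile the treatment duration in section 6 with the visit windows in section 8, and state the anchor of the TOC window. Define TOC so that it falls after EOT for every patient and by the same rule in both arms. Two definitions would do this:

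- **A fixed interval after the last dose.** This equalises time off drug, at the price of a calendar day that varies with course length.
- **A fixed study-day window from randomisation that opens after the last permitted treatment day.** This keeps the calendar day the same and removes on-drug assessment. Time off drug would still differ by about 10 days between 4-day and 14-day courses (14 − 4).

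Only the timing of assessment changes; the permitted treatment duration is for the sponsor to confirm, and no change to it is proposed here.

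The cost is an amendment to one visit definition and a later clinical and microbiological assessment for some patients. That assessment should not be assumed to come free with the existing follow-up, because the day-30 data in Table 3 cover survival and organisms identified, and no clinical-cure visit is shown at that time. Visits made at the wrong time cannot be repaired in the analysis, so the change is best made before further patients reach TOC.
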